**Figure 1 F1:**
[figure not shown]
Randomization procedure.

In addition, for families in the FG-c condition, it will be assessed (1) whether a FG-c coordinator explained the concept of a FG-c; (2) whether an FG-c has taken place, (3) whether a plan has been formulated; and (4) whether the plan has been carried out (at the moments when posttests at 1, 3 and 6 months after the FG-c have been carried out). To diminish the burden that is imposed on families as much as possible, measurements at 1 and 3 months will be done as much as possible by telephone.

The design of this study is approved by the independent Ethical Committee of the Faculty of Social and Behavioral Sciences of The University of Amsterdam (approval number: 2013-POWL-3308).

### Study sample

We aim to include *N* = 300 families, who will be randomized in a 2 (FG-c): 1 (control group) ratio to ensure that there is enough power to also conduct the planned moderator analyses. These groups are large enough to detect effects of FG-c’s.

Given the goal of YCAA to carry out 800 FG-c’s each year, the inclusion of 300 families will be completed within six months. This sample size is sufficient to test the hypotheses with an alpha of .05 and a small to medium effect (*d* = .35). FG-c can be used for all families, so there are no exclusion criteria in this study.

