### Design

A randomized Controlled trial will be conducted to examine whether FG-cs are effective in changing: (1) child’s safety (i.e., decrease in (risk for) abuse/neglect; less supervision orders or shorter supervision order; less or shorter out of home placement); (2) the involvement of the broader social network; (3) perceived control over the problems in the families, empowerment of parents; improvement of family functioning; (4) less use of professional care. A second aim is to study whether the effectiveness of FG-c is influenced by characteristics of the implementation of the methodology, characteristics of the family managers (such as education, or attitude towards FG-c), or by family characteristics (such as size of the social network, ethnicity or family type: single/married).

Using computerized randomization two comparable groups will be formed. Until the inclusion of 300 families is completed (presumably within 6 months), every family starting care at Youth Care Agency Amsterdam (YCAA) will be randomly allocated to care with or without a Family Group conference. Because allocation to care with a FG-c will not always result in an actual Family Group conference and/or an approved Family Group plan, 200 families will be assigned to care with FG-c and 100 families to care without FG-c. Five multi-informant/source (parent, family manager; FG-coordinator; member of the family’s social network; child (if > 8 years of age), and file analysis) assessments will be carried out in both groups. Pre-tests will take place before FG-cs starts. Subsequently, in both groups post-tests will be carried out 1, 3, 6 and 12 months after the FG-c has taken place (see also Figure 1 for the flow chart).

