### Statistical analyses

Missing data will be imputed so that all participants will be included in the analyses, and using LISREL 8.8, the multiple imputation will be carried out by the expectation maximization algorithm [37]. Both an intention to treat as well as a completer analysis will be performed.

In order to examine the effectiveness of FG-c overall effectiveness will be examined for all outcome measures by conducting an ANCOVA, with the outcome measures at post-test as dependent variables, treatment condition as factor and pre-intervention scores of the outcome variables as co-variates, as is recommended for RCTs using pre- and post-tests [38]. Effect sizes will be computed as Cohen’s d, based on adjusted means and standard errors.

For categorical moderator analyses, the same ANCOVA’s will be conducted, with the moderators as factor. Post-hoc analyses for moderator effects will be conducted by splitting the file according to the moderator and again conducting an ANCOVA and calculating effect sizes separately for each group. Regression analyses will be conducted for the continuous moderators.

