## Discussion

The implementation of Family Group-conferencing for decision making in child welfare has gained popularity rapidly. In The Netherlands, a change in youth protection is proposed for 2015 according to which the law states that every family has the right to start child care with making their own plan. The philosophy of a society in which everyone can participate and has the right to make its own decisions is the background of this development. Question is, however, if every family is able to make its own plan, and if these plans are effective in terms of increased child safety, increased commitment of the social network, if families are able to gain control over their own help, if family functioning improves and use of professional care decreases. The present study addresses this by examining the effectiveness of FG-c by means of a randomized controlled trial. Worldwide, despite an overload of studies examining FG-c [16], there are only six studies that examined FG-c with a comparable comparison group [15]. It is thus of crucial importance to conduct a RCT of FG-c, including sufficient participants as the present study intends to achieve.

Moreover, few RCTs have been conducted of FG-c, even less so examine for whom, under what conditions FG-c is likely to be most effective, as the present study does by carefully examining implementation, method and participant characteristics.

The present study thus has several strenghts: several strengths: it will extend the knowledge on Family Group-conferencing as a decision making procedure in child care. By using a randomized controlled trial, confounding variables are excluded as much as possible. A sufficiently large sample size will be used to study effectiveness as well as moderators of the effectiveness.

Moreover, a multi-informant approach will be used by asking parents, family managers, FG coordinators, a member of the network and children (if older than 8) to report on the outcomes and by conducting file-analysis.

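### The claim that 300 families at 2:1 give enough power for the moderator analyses is not supported by the plan's own d = .35 for moderators measured in both arms

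*Protocol article*

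**What the plan says.** All references are to the protocol article.

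- **Study sample** sets the size ("We aim to include *N* = 300 families") and says that families will be "randomized in a 2 (FG-c): 1 (control group) ratio to ensure that there is enough power to also conduct the planned moderator analyses". It adds "These groups are large enough to detect effects of FG-c’s" and "This sample size is sufficient to test the hypotheses with an alpha of .05 and a small to medium effect (*d* = .35". It gives no power figure, moderator effect size or subgroup share.
- **Design** fixes the arms ("200 families will be assigned to care with FG-c and 100 families to care without FG-c") and gives another reason for the ratio: "Because allocation to care with a FG-c will not always result in an actual Family Group conference and/or an approved Family Group plan".
- **Statistical analyses** plans an ANCOVA with "treatment condition as factor and pre-intervention scores of the outcome variables as co-variates". Categorical moderators enter the same model as a factor, with split-file follow-up. Continuous moderators are handled by regression. Both an intention-to-treat and a completer analysis are planned.
- **Discussion** lists as a strength: "A sufficiently large sample size will be used to study effectiveness as well as moderators of the effectiveness".

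The opening of Methods and design makes moderators the second of the two main research questions. The moderators are of two kinds. Family and family-manager characteristics exist in both arms. Program integrity and conference and coordinator characteristics exist only in the FG-c arm.

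**The concern.** A sample sized for a main effect usually has far less power for an interaction of the same size. Here the same 300 families and the same d are offered as adequate for both. The ratio is also presented as the means of securing moderator power. At a fixed total, however, equal arms minimise the variance of the treatment contrast and of its interaction with a moderator present in both arms.

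The moderator results are meant to show for whom the conference works. If readers rely on the stated adequacy, a non-significant interaction could be taken as evidence of similar benefit across families, when the test had little chance of finding a difference as large as the planned overall effect.

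**Working it through.** **Inputs from the article:** 200 FG-c families, 100 control families, alpha .05, d = .35, ANCOVA on the pre-test score.

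**Assumptions, because the article gives no figure:** two-sided test; 80% power as the meaning of sufficient; binary moderator split 50/50, 30/70 or 20/80; pre-post correlation r from 0 to .7; complete data unless stated. Outcome SD is 1. Power is taken as Φ(effect/SE − 1.96); noncentral t gives the same values to within half a percentage point.

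**1. The plan's own figure.** SE = √(1/200 + 1/100) = 0.1225. Then 0.35/0.1225 = 2.86, and power is 81.5% (noncentral t 81.3%). For 80% power at 2:1, the control arm needs 1.5 × (2.80/0.35)² ≈ 96.1, so 97, or 291 families in total. The 300 therefore reproduces as a main-effect sample size. At 150:150 the power is 85.8%.

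**2. Interaction with a binary moderator present in both arms.** With share f in one level, SE = √(1 − r²) × √[(1/200 + 1/100)(1/f + 1/(1 − f))].

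- f = .5, r = 0: SE = √(0.015 × 4) = 0.245; 0.35/0.245 = 1.43; power 29.8%.
- f = .3, r = 0: SE = √(0.015 × 4.76) = 0.267; power 25.8%.
- f = .2, r = 0: SE = 0.306; power 20.8%.
- f = .5, r = .5: SE = 0.212; power 37.8%.
- f = .5, r = .7: SE = 0.175; power 51.6%.
- f = .5, r = 0, 20% dropout: power 24.8%.
- f = .5, r = 0, one-sided test: power 41.4%.

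**3. Smallest interaction with 80% power** is 2.80 × SE. For f = .5 this is 0.69 SD at r = 0, 0.59 SD at r = .5 and 0.49 SD at r = .7. For f = .3 and r = 0 it is 2.80 × 0.267 = 0.75 SD. Reaching 80% power for a 0.35 SD interaction (f = .5, r = 0) would take about 1,153 families at 2:1 or 1,025 at 1:1.

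**4. Split-file follow-up.** With half the sample (100 and 50 families), d = .35 has 52.4% power at 2:1 and 57.3% at 1:1.

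**5. Effect of the ratio at 300 families.**

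| Test (effect 0.35 SD, r = 0) | 200:100 | 150:150 |
|---|---|---|
| Main effect | 81.5% | 85.8% |
| Interaction, both arms, 50/50 | 29.8% | 32.9% |
| FG-c arm only, 50/50 | 69.7% | 57.3% |

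In the last row SE = √(1/100 + 1/100) = 0.141 with 200 families and √(1/75 + 1/75) = 0.163 with 150. At r = .5 that row becomes 81.5% against 69.7%. It assumes that every family in the arm contributes; families without a conference have no conference characteristics to analyse, so for those variables the figures are upper limits.

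**The case against.** Four points on the other side have weight.

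- **The ratio reason is partly right.** A reader might infer that 2:1 lowers power for every moderator analysis. It does not. Program integrity, conference and coordinator characteristics are observed only in the FG-c arm, and there 200 families clearly beat 150. The reason fails only for moderators present in both arms.
- **No moderator effect size is stated.** A reader might infer that the power claim is simply false or that the sizing arithmetic is wrong. The arithmetic for d = .35 reproduces, and an interaction of 0.70 SD would have about 81% power. What can be said is that the claim has no support at the only effect size the article gives.
- **Simple t-test figures understate an ANCOVA.** This stands. At r = .5 main-effect power is 91%, not 81%. Yet a 0.35 SD interaction with a balanced moderator stays at 52% or below over r from 0 to .7. Nor do the interaction figures carry over directly to continuous moderators: the SE of an interaction slope per SD of moderator is about 0.124, close to the main-effect SE, though on a different scale.
- **Non-uptake.** A reader might infer that the Design section claims 2:1 protects the intention-to-treat test. It makes no such claim. A completer analysis is also planned, and for it 2:1 equals 1:1 when half the FG-c arm holds a conference and is better below that (at 40%: 64.6% against 63.0%).

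The analysis plan is not shown and may treat moderators more fully. That does not answer the point, because the article states adequacy outright in two places.

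**Conclusion.** The point holds for moderators measured in both arms. The stated alpha and d support about 81% power for the main effect. They give about 30% for an equally large interaction with a balanced binary moderator, 21% to 26% for uneven splits, and 38% to 52% with a pre-post correlation of .5 to .7. The detectable interaction is about 0.69 SD (0.59 at r = .5), roughly twice the d on which the trial is sized. For these tests and for the main effect the 2:1 ratio costs a few percentage points, so it cannot secure their power. It does help moderators that exist only in the FG-c arm.

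The figures rest on a two-sided test, an 80% target, and assumed subgroup shares, correlations and dropout. The conclusion does not change within the ranges shown. It does not extend to the main-effect sample size, which reproduces. Nor do the documents say that null interactions will be read as equal benefit; that is a risk the present wording invites.

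**What to change.** 1. In Study sample and Discussion, limit the adequacy statement to the main effect: 200 and 100 families give about 81% power, two-sided .05, for an intention-to-treat d = .35 with complete data and no covariate gain. Note that ANCOVA raises this figure and that dropout and non-uptake of the conference lower it. For example, 20% dropout without covariate gain gives 72%.
2. State the detectable treatment-by-moderator interaction: about 0.7 SD for a balanced binary moderator, or about 0.6 SD if r = .5. Label these tests exploratory, and say that a non-significant interaction is not evidence of equal benefit.
3. Limit the moderator reason for 2:1 to moderators observed only in the FG-c arm, keep the non-uptake reason from Design, and make the two sections give the same account.

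The cost is wording only, with no additional families and no change to the analyses. The drawback is that the stated figures become less favourable.

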### Recruitment

Participants are recruited at Youth Care Agency Amsterdam and Surroundings (YCAA). When a family is referred to YCAA, a first step is to establish whether the family indeed belongs to the target group of YCAA. If that is the case, a YCAA manager determines whether the need for help is urgent. If this is the case, the family is immediately assigned to a personal family manager and is informed about the study. In this stage, randomization takes place, active informed consent is received and both youth care and the study will start. If the situation is less urgent, families may be placed on the waiting list. For those families, informed consent, randomization and start of youth care will be postponed until the waiting list period has expired. Specifics on the flow of participants are graphically presented in Figure 1.

### Conditions

#### ***Family group- conference [in Dutch: Eigen Kracht-conferentie]***

A Family Group - conference (FG-c) is defined as an approach to care that allows citizens to keep responsibility over decisions on issues within the family, neighborhood, or group of people in which they operate (Oosterkamp Szwaycer et al., 2012). FG-c provides citizens the opportunity to make a plan, using their own capabilities and by using support from outside. This research will focus on FG-cs that are used in youth care as a decision-making model in which families together with others in their social network, such as extended family, neighbors, friends and others, make a plan to solve their problems. The responsibility for making the plan lies within the (extended) family and the social network. Professionals are involved only in order to determine whether the plans developed by the family group are sufficiently safe for the children and to provide information about professional help options.

The Program Bureau responsible for FG-cs (in Dutch: Eigen Kracht Centrale), a national organization that supports and performs FG-c’s, organizes the family group conferences. The FG-c Program Bureau organizes the recruitment and training of the FG coordinators and contracts FG coordinators for the duration of a conference. Family managers thus request a FG-c at the FG-c Program Bureau. The FG coordinator organizes the FG-c in close cooperation with the family and family manager. The FG coordinator is independently associated with the FG-c Program Bureau and is thus not employed by a professional youth care facility.

A FG-c consists of two phases: the first phase is preparation (activation phase): after referral (or self-referral) to a FG-c, the independent FG coordinator contacts stakeholders (family, important people for the family, professionals) and prepares the conference. The coordinator organizes a time and location in accordance with the family’s wishes and is responsible for all practical coordination. The second phase is the conference phase: professionals share information on the needs and care options during the actual conference. Additionally, professionals provide, if necessary, conditions for the FG plan. The meeting consists of the information phase, a private part and the presentation of the plan. During the private part, no professional youth care workers or FG coordinator is present. During the private part, the care plan is developed. During the presentation phase, the care plan is tested to ensure safety: the safety of the children in the family has to be guaranteed and approved upon by the family manager. If a plan has been developed, the FG-coordinator places the responsibility for implementation of the plan with the family and the broader social network.

The plan is the starting point for care and there is no other treatment plan next to it. The family manager monitors the implementation of the plan and ensures that the agreements are carried out as intended in contact with the responsible member of the social network. This procedure is similar to the usual case management conducted by YCAA, with the difference that with regard to an FG-c plan, the network is responsible for the implementation of the plan, whereas in usual care, this is the responsibility of the family manager. In addition, at each conference, there is a contact person (or more) from the social network of the family who contacts a family manager to organize a new FG-c when things do not proceed according to plan. Thus, both the social network and the ‘helpers’ (can be someone else than the family manager) have a role in the implementation of the plan, the process of cooperation and adaptation of the plan to the developments occurring after the conclusion of the plan.

### Control condition

In the control condition, the family will receive the usual care. This means that the family manager is the one who designs and organizes the care plan instead of the family. YCAA works according to Generic Family oriented method since 2011: child protection, juvenile probation and youth are no longer distinguished. Employees (former youth probation workers, youth care workers and child protection workers) have been retrained as family managers (FM), who are able to provide the needed care to a family (or by referring to other professional services). As in the experimental condition, in the control condition, family managers will also work with a care plan. The difference between the FG-c and the control condition lies in the manner in which the plan is established: In the control condition, this is done by the family manager, along with parents/family, they discuss problems in the family and formulate goals, strict agreements are made on what professional help will be started. Within the FG-c, the plan is made by the family and social network. In a Family Group plan, they explain how they see the solution to their problems and what steps they will undertake to solve the problems, including starting professional care. In the intervention and control conditions, the role of the family manager is actually the same: a family manager works in both conditions with the care plan that has been developed, however, the levels of control differ: in the FG-c condition, control over the plan is with the family, in the TAU condition, control is with the family manager.

### Instruments

An overview of the concepts, instruments and sources of information is presented in Table 1. At the 5 assessment points, the family manager, a member of the network, parent, the family group coordinator and the child (if older than 8 years) will be asked to answer questions, either online, or by telephone. The families and child will receive assistance when filling out the questionnaires.

**Table 1 T1:** Concepts, instruments and informants at the different assessment points

	**Domain/concept**	**Instrument**	**Test**					**Source**					
			**T1**	**T2**	**T3**	**T4**	**T5**	**FM**	**MN**	**P**	**FGC**	**R**	**C**
Primary outcome													
	Safety	LIRIK	x		x	x	x	x	x				
		Safety line	x	x	x	x	x	x					
		CAPI	x		x		x	x	x	x			
		Succint		x		x	x	x	x	x			
Secondary outcomes													
	Commitment	PSQ	x	x	x	x	x	x		x			
		ISEL	x	x^1^	x^1^	x	x	x					
		Succint	x	x^1^	x^1^	x	x	x		x			
	Control/empowerment	Interview	x	x	x	x	x	x	x	x			
		Succint	x	x	x	x	x	x					
		FES	x	x^1^	x^1^	x	x	x					
	Family functioning	PSI	x^1^	x^1^	x^1^	x^1^	x^1^		x				
		Succint	x	x	x	x	x	x					
		FES	x	x^1^	x^1^	x	x	x					
	Family functioning	PSI	x^1^	x^1^	x^1^	x^1^	x^1^			x			
	Professional care	File research	x	x	x	x	x					x	
Cost- effectiveness	Costs	Cost questionnaire	x			x	x			x			
Moderators													
Characteristics implementation FG-c and family manager	Number of families	Registration form	x	x	x	x	x					x	
	Role FM	Registration form		x	x	x	x	x	x	x	x	x	
	Chacareristics FM	Registration form	x									x	
	Time to FG-c	File analysis	x	x								x	
	Number members network at FG-c	Registration form		x							x	x	
	Phases FG-c/plan carried out as intended	Registration form	x	x	x	x		x			x	x	
Characteristics families	Demograpgics	File research/questionnaire	x	x	x	x	x	x		x		x	
	Risk factors	Risk factors List	x					x		x		x	
	Problems child	BPC (if child > 8)	x			x	x						x

*Note*: T1 = pretest (questionnaire); T2 = post-test after 1 month (interview by telephone); T3 = post-test after 3 months (interview by telephone); T4 = post-test after 6 months (questionnaire); T5 = follow-up assessment after 12 months (questionnaire); FM = Family Manager; MN = member network; P = Parent; FG-c = Family Group-conference; FGC = Family Group Coordinator; R = researcher; C = Child; ^1^ = selection of the original instrument.

### Primary outcomes

The primary outcome is child safety. This outcome will be assessed by using various child safety indicators. First, to measure whether the safety in families has increased the Light Instrument to assess Risk of Child Abuse (Lirik) [21] will be used at all assessment points. This instrument is filled out by the Family manager. The Lirik is widely used in the Netherlands and is a standard procedure for the YCAA family managers.

Additionally, after each case management meeting, family managers fill out the ‘safety line’ of the family. Families are given a safety score between 1 and 10. This is a new measurement method, used by YCAA as standard practice. These multiple assessment points allow to detect changes in safety over time.

Furthermore, parents will be asked to fill out the Child Abuse Potential Inventory short version (CAPI) [22]. This is a widely used instrument to identify child abuse potential [23]. A Dutch version has been translated and validated by Grietens, De Haene, and Uyttebroek [24].

The “Success of Intervention Inventory”(Succint) will be used to evaluate the success of the intervention (care with or without FG-c). This questionnaire measures whether changes are visible in safety, perceived control and social support/cohesion. The Succint has been developed by PiResearch, especially to evaluate the success of FG-c [8]. This instrument will be filled out by a parent, family member, and family manager.

